### Outcome Measurement

Given the long duration and multi-modal nature of the interventions, a range of outcome measures will be used to ensure evaluation of relevant variables that span the domains of the International Classification of Functioning [66]. The variables and measurement tools that will be employed are summarized in Table 1. These measures were selected based on the primary and secondary aims of the trial, clinical relevance, psychometric qualities, and feasibility (availability, cost and administration time). Evaluations will be conducted over a 2-day assessment period at baseline, post-intervention, six months, and 12 months by trained assessors blinded to knowledge of study hypotheses and group assignment. At each assessment the assessors will be asked to record their 'guess' as to the group assignment of each participant.

**Table 1 T1:** Outcome variables, measurement tools and assessment schedule

Variable	Measurement tool	Baseline	Post-intervention	6-month follow-up	12-month follow-up
*Primary measures*					

Blood pressure	Sphygmomanometer [67]	√	√	√	√

Waist girth	Tape measure [68]	√	√	√	√

Lipid profile*	Biochemical analysis	√	√	√	√

Fasting serum glucose	Biochemical analysis	√	√	√	√

Haemoglobin A1c	Biochemical analysis	√	√	√	√

*Secondary measures*					

Aerobic fitness	Peak VO_2 _using maximal treadmill stress test (ramp protocol)	√	√		√

Lower extremity function	Short Physical Performance Test [69]	√	√	√	√

Walking endurance	Six-Minute Walk Test [70]	√	√	√	√

Physical activity	Step Watch™accelerometers	√	√		√

	International Physical Activity Questionnaire [71]	√	√	√	√

Fatigue levels	Fatigue Assessment Scale [72]	√	√	√	√

Cognition	Montreal Cognitive Assessment [73]	√			√

Mental health	Hospital Anxiety and Depression Scale [74]	√	√	√	√

Quality of sleep	Pittsburg Sleep Quality Index [75]	√	√	√	√

Tobacco use	Self-report, using a health passport	√	√	√	√

Health care utilization	Self-report, using a health passport	√	√	√	√

Medication adherence	Self-report, using a health passport	√	√	√	√

Health-related quality of life	Medical Outcomes Study Short-form 36-item Questionnaire [76]	√	√		√

Health-related goals	Goal Attainment Scaling [77]	√	√	√	√

Secondary vascular events**	Health record abstraction	√	√	√	√

*Includes total cholesterol, high-density lipoprotein cholesterol (HDL-C), low-density lipoprotein cholesterol (LDL-C), triglycerides

**Includes second stroke, second TIA, acute coronary syndrome (i.e., unstable angina and myocardial infarction), heart failure, and vascular death

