**Methods/Design:**

A single blind, randomized controlled trial will be conducted at two sites to compare the effectiveness of a program of rehabilitative exercise and education versus usual care in modifying vascular risk factors in adults after NDS/TIA. 250 adults within 90 days of being diagnosed with NDS/TIA will be randomly allocated to a 12-week program of exercise and education (PREVENT) or to an outpatient clinic assessment and discussion of secondary prevention recommendations with return clinic visits as indicated (USUAL CARE). Primary outcome measures will include blood pressure, waist circumference, 12-hour fasting lipid profile, and 12-hour fasting glucose/hemoglobin A1c. Secondary measures will include exercise capacity, walking endurance, physical activity, cognitive function, depression, goal attainment and health-related quality of life. Outcome assessment will be conducted at baseline, post-intervention, and 6- and 12-month follow-ups. Direct health care costs incurred over one year by PREVENT versus USUAL CARE participants will also be compared. Ethical approval for the trial has been obtained from the relevant Human Research Ethics Boards.

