### Interventions

#### USUAL CARE Intervention

Following completion of the acute management of TIA and NDS, USUAL CARE participants will be referred to the site's outpatient Neurovascular Clinic, staffed by neurologists/internists and nurses, for a neurological and health assessment, counselling regarding stroke/TIA and diagnostic test results, and assessment, modification and education of secondary prevention factors (i.e., dietary intake, lipid profile, adherence to medication regime, physical activity, smoking, alcohol intake, elf-referral to weight loss and smoking cessation programs) [78]. Required therapeutic interventions will be initiated or adjusted (e.g., medications, diagnostic/laboratory tests) and referrals will be sent to appropriate team members or clinics (e.g. social worker, physiotherapist, occupational therapist, dietician, speech language pathologist, diabetes clinic, hypertension clinic, anticoagulation clinic, smoking cessation program). Follow-up care will be provided by return clinic visits, with an average of three visits in total. Those patients who no longer require follow-up will be referred back to their primary care physician.

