#### PREVENT intervention

After completing the acute management of TIA and NDS, PREVENT participants will participate in a multi-modal, case-managed program of exercise and education. Because this intervention is behavior-focused (e.g., encouraging daily physical activity, health eating, smoking cessation, medication use adherence), several strategies known to facilitate and sustain behavioral change have been incorporated into the design [79,80]:

(i) Each participant will meet with the PREVENT physicians and program providers to identify personal goals/barriers/possible solutions related to risk factor targets and lifestyle modifications, based on the baseline assessment and the participant's needs and values.

(ii) Each participant will be provided with a user-friendly health passport in which the participant and PREVENT staff will maintain documentation regarding health-related appointments, assessment results, medications, BP, cigarettes smoked, lipid profile, blood glucose, body weight, waist circumference, daily physical activity, dietary intake, as well as goal attainment related to these domains. All information in the passport will be written in 'plain language' (i.e., Grade 8 reading level).

(iii) Use of positive reinforcement (encouragement, positive feedback).

(iv) Use of adult learning strategies (interactive educational sessions, participant involvement in content selection).

(v) After completion of the formal program, telephone follow-up will be implemented (see below). In addition, individual therapeutic interventions will be initiated or adjusted, as described above for usual care.

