##### Post-program follow-up

After the 12-week program, PREVENT participants will be provided with a written maintenance program based on their long-term goals. Participants will be requested to maintain their health passport and will be phoned monthly by the site coordinator until the 12-month follow-up as a means of monitoring of use of health passport, health status, health care utilization and adherence to the maintenance program.

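### Three secondary outcomes are recorded in the health passport, which is described only as part of PREVENT, so ascertainment may differ between arms

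*Protocol article*

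**What the plan says.** Table 1 (Outcome Measurement) lists tobacco use, health care utilization and medication adherence as secondary measures. For each the tool is "Self-report, using a health passport", ticked at baseline, post-intervention, 6 months and 12 months, with no distinction by arm. No other tool is listed for these three.

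The passport itself is introduced under the PREVENT intervention, where "several strategies known to facilitate and sustain behavioral change have been incorporated into the design". It is item (ii) of that list: "Each participant will be provided with a user-friendly health passport in which the participant and PREVENT staff will maintain documentation regarding health-related appointments". Medications and cigarettes smoked are also among its listed contents.

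Under Post-program follow-up, PREVENT participants are asked to keep the passport going and "will be phoned monthly by the site coordinator until the 12-month follow-up". The stated purpose of these calls includes checking that the passport is used and tracking the participant's use of care.

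The USUAL CARE Intervention section describes clinic assessment, counselling and referral. On later contact it says: "Follow-up care will be provided by return clinic visits, with an average of three visits in total". It mentions no passport and no telephone calls.

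The Abstract states: "Direct health care costs incurred over one year by PREVENT versus USUAL CARE participants will also be compared". The Background repeats this as secondary aim (iii). Neither place, nor the Discussion, names the data source for costs.

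**The concern.** An outcome should be recorded in the same way, at the same contacts and with the same effort in both arms. Here the recording tool for three outcomes is also listed as a strategy of the experimental intervention. The added effort (staff entries, monthly prompting) is described for one arm only. A between-arm difference in recorded visits, cigarettes or adherence could then reflect a difference in recording rather than in behaviour or use of care.

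Tobacco use and medication adherence belong to secondary aim (i). Utilization is the obvious input to the cost comparison in aim (iii), and Table 1 shows no source for it other than the passport. If recording differs by arm and there is no second source common to both, no analysis can separate a true difference from a recorded one.

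**Working it through.** The document gives no figure on this point to reproduce. The check sets the sections side by side.

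**1. Is the passport common to both arms?**
- Table 1 implies that it is. It makes no distinction by arm, and it ticks the passport measures at baseline.
- Randomization Procedures says that allocation is revealed after the baseline assessment. A tool issued as part of PREVENT cannot supply a baseline value.
- The PREVENT section implies that it is not. The passport is one of the intervention's listed strategies, and PREVENT staff co-maintain it. Post-program follow-up asks PREVENT participants to continue it.
- The USUAL CARE section is silent.

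These passages do not fit together and must be reconciled.

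**2. Does either reading remove the problem?**
- *Only PREVENT holds a passport.* The tool in Table 1 does not exist for USUAL CARE, whose data must come by some other, unstated route.
- *Both arms hold a passport.* Controls receive something that the article classes as a behaviour-change strategy. Staff entries and monthly calls are still described only for PREVENT, so recording is still more intensive there. If the 12-month follow-up is counted from baseline, the calls cover roughly 12 − 3 = 9 months.

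Neither reading gives equal ascertainment as the article is written.

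**3. Which outcomes are touched?**
- Touched: tobacco use, health care utilization and medication adherence, and the cost comparison if it draws on passport utilization.
- Not touched: the primary outcomes (blood pressure, waist girth, lipids, glucose, haemoglobin A1c), which are measured directly, and secondary vascular events, which Table 1 takes from health record abstraction.

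**4. Can the size be found?** Suppose true utilization is equal, PREVENT captures a share *a* of contacts and USUAL CARE a share *b*. The apparent ratio of PREVENT to USUAL CARE is then *a*/*b*. All the shares below are assumptions, and none comes from the document.

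| *a* (PREVENT) | *b* (USUAL CARE) | *a*/*b* | PREVENT appears |
|---|---|---|---|
| 0.95 | 0.95 | 1.00 | equal |
| 0.95 | 0.90 | 1.06 | 6% higher |
| 0.95 | 0.80 | 1.19 | 19% higher |
| 0.95 | 0.70 | 1.36 | 36% higher |
| 0.90 | 1.00 | 0.90 | 10% lower |

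Modest differences in capture would produce an apparent difference in use of care. Both its size and its sign depend on capture rates that the article does not give.

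**The case against.** The strongest reply has four parts.

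- **No passage denies USUAL CARE a passport.** Table 1 applies it without distinction and before allocation is known. The USUAL CARE section describes clinical care, so its silence on data collection is weak evidence. This stands: it is not established that the arms use different tools. It does not remove the point, because staff entries and monthly calls remain specific to PREVENT.
- **No passage says that costs come from the passport.** This also stands. A reader might infer that the cost comparison is biased against PREVENT because its contacts would be recorded more fully. The article supports neither the link to costs nor the direction. It also calls the cost comparison preliminary.
- **Outcome assessors are blinded, and participants cannot be.** Table 1 sits within a schedule carried out by blinded assessors, and self-report by unblinded participants is unavoidable in this design. A reader might infer that smoking and adherence are recorded with treating staff and so are biased in favour of PREVENT. The listed passport contents include cigarettes and medications but not adherence as such, so that is not shown.
- **An article condenses data-collection detail.** This is true in general. Here, however, the article does state the measuring tool, and what it states conflicts with its own description of that tool.

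**Conclusion.** The point holds as a risk of differential ascertainment for tobacco use, health care utilization and medication adherence. It extends to the one-year cost comparison only to the extent that passport data feed it. It rests on two things the article states: the passport is the only listed tool for these outcomes, and the staff entries and monthly monitoring calls that support it are described for PREVENT alone. It does not depend on whether USUAL CARE participants also hold a passport.

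Size and direction cannot be determined from the document, and the tabulated ratios only show how the result depends on assumed capture. The primary outcomes and record-abstracted vascular events are unaffected. Severity is moderate: three secondary outcomes and a preliminary cost comparison are at risk, and the remedy is cheap.

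**What to change.** 1. Reconcile Table 1 with the intervention sections. State whether both arms receive the passport and how the baseline values are obtained.
2. Do not use the passport or the monthly calls as an outcome source. Collect tobacco use, medication adherence and health care contacts with one identical form in both arms at the four existing assessments.
3. Add admissions, emergency visits and clinic visits to the health-record abstraction already planned for vascular events, in both arms. Name that abstraction as the source for costing.
4. Keep passport and call data as process measures of intervention delivery.

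**Cost.** A short form at existing visits and a few more abstraction fields. The intervention itself does not change.

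**Downsides.**
- Self-report will not become fully equal, because PREVENT participants still keep the passport and receive calls. Record abstraction equalises capture only for the contacts it covers.
- Asking about contacts may reveal allocation to the assessor. The form should therefore exclude PREVENT sessions or be given after the other blinded assessments.

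The article reports that the trial is enrolling, so the change is worth making early: contacts not recorded alike in both arms may not be fully recoverable later.

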### Interventions

#### USUAL CARE Intervention

Following completion of the acute management of TIA and NDS, USUAL CARE participants will be referred to the site's outpatient Neurovascular Clinic, staffed by neurologists/internists and nurses, for a neurological and health assessment, counselling regarding stroke/TIA and diagnostic test results, and assessment, modification and education of secondary prevention factors (i.e., dietary intake, lipid profile, adherence to medication regime, physical activity, smoking, alcohol intake, elf-referral to weight loss and smoking cessation programs) [78]. Required therapeutic interventions will be initiated or adjusted (e.g., medications, diagnostic/laboratory tests) and referrals will be sent to appropriate team members or clinics (e.g. social worker, physiotherapist, occupational therapist, dietician, speech language pathologist, diabetes clinic, hypertension clinic, anticoagulation clinic, smoking cessation program). Follow-up care will be provided by return clinic visits, with an average of three visits in total. Those patients who no longer require follow-up will be referred back to their primary care physician.

#### PREVENT intervention

After completing the acute management of TIA and NDS, PREVENT participants will participate in a multi-modal, case-managed program of exercise and education. Because this intervention is behavior-focused (e.g., encouraging daily physical activity, health eating, smoking cessation, medication use adherence), several strategies known to facilitate and sustain behavioral change have been incorporated into the design [79,80]:

(i) Each participant will meet with the PREVENT physicians and program providers to identify personal goals/barriers/possible solutions related to risk factor targets and lifestyle modifications, based on the baseline assessment and the participant's needs and values.

(ii) Each participant will be provided with a user-friendly health passport in which the participant and PREVENT staff will maintain documentation regarding health-related appointments, assessment results, medications, BP, cigarettes smoked, lipid profile, blood glucose, body weight, waist circumference, daily physical activity, dietary intake, as well as goal attainment related to these domains. All information in the passport will be written in 'plain language' (i.e., Grade 8 reading level).

(iii) Use of positive reinforcement (encouragement, positive feedback).

(iv) Use of adult learning strategies (interactive educational sessions, participant involvement in content selection).

(v) After completion of the formal program, telephone follow-up will be implemented (see below). In addition, individual therapeutic interventions will be initiated or adjusted, as described above for usual care.

##### Group exercise component

75-minute group exercise sessions, lead by a physiotherapist or kinesiologist, will be held twice weekly for 12 weeks. The sessions will involve (i) 5-10 minutes of warm-up exercises, (ii) 15 minutes of progressive resistance training of major extremity muscles, (iii) 30 minutes of aerobic training consisting of three 10-minute stations of treadmill walking, stationary cycling and stepping at an initial intensity of 40-70% of heart rate reserve, as determined by stress test results; (iv) 5-10 minutes of cool-down exercise; (v) progressive resistive strengthening of major upper and lower extremity muscle groups. Heart rate will be continuously monitored, and BP and blood sugars will be measured before and after exercise, as indicated. Both strengthening and aerobic training will be prescribed and progressed according to ACSM guidelines [64].

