#### Sample Size

Systolic blood pressure, the most robust predictor of secondary vascular events [14], was selected as the outcome variable for sample size calculation. Using estimates obtained from our pilot study, a sample size of 119 in each group will have 80% power to detect a difference in means of 4.9 mmHg, assuming that the common standard deviation is 13.4 using a two group t-test with a 0.05 two-sided significance level. We have allowed for an overall attrition rate of 5% [55], thus increasing the sample size to 125 per group (250 in total). The trial will not be sufficiently powered to determine the effectiveness of the PREVENT intervention in reducing recurrent TIA, stroke or cardiac events. Thus, it will be exploratory in this regard and will help inform the design of a future, more extensive trial.

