##### Home exercise component

Group exercise sessions will be supplemented by 30 minutes of home cardiovascular exercise, 3-4 days/week at a rating of perceived exertion (RPE) of 3-5 on the Borg 0-10 scale [81,82].

***Education component ***One 1.5-hour group session will be conducted weekly by a multi-disciplinary team of health professionals. The schedule for the educational sessions and topics of discussion are outlined in Table 2. Family members/caregivers of participants will be encouraged to attend. Powerpoint slides will be used to ensure consistency of information across sites. Participants will also have access to scheduled grocery shopping tours and cooking demonstrations to further support program objectives.

**Table 2 T2:** Schedule and discussion topics for educational sessions.

Week 1	Heart healthy eating: The basics
Week 2	Setting of health-related goals

Week 3	Exercise: The basics

Week 4	Cardiovascular risk factors and BP self-monitoring

Week 5	Nutrition: Building on the basics (including a 3-day food record analysis by the dietician)

Week 6	Exercise: Building on the basics

Week 7	Cardiovascular medications

Week 8	Healthy weight

Week 9	Smoking cessation

Week 10	Stress & coping

Week 11	Fine-tuning healthy eating

Week 12	Wrap-up

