### Data management and analysis

Data collected at each site will be recorded on standardized forms and entered into a secure database using a centralized, web-based data entry system that contains quality control checks (e.g., range checks, notification of missing data). An independent Data Safety and Monitoring Board, consisting a cardiologist, neurologist and a statistician, has been set up to review mid-point results (or at any time that a serious adverse event occurs) and inform the investigators on issues of trial safety.

Descriptive statistics will be calculated for dependent and independent variables. Demographic and clinical characteristics of subjects in the experimental and control groups will be compared on admission using 2-sample t-tests (continuous data) and Chi-square analysis (nominal data). Nonparametric methods will be used when assumptions of normality are violated. Similar analyses will be used to compare characteristics of (i) patients who consent to participate versus those who do not; (ii) subjects who complete the study versus those who withdraw, in order to determine the representativeness of the sample. A mixed effects analysis of variance with repeated measures will be used to model the treatment effects for variables that are interval or ratio and conform to the assumptions of normality (i.e., BP, waist girth, total cholesterol, HDL-C, LDL-C, triglycerides, serum glucose, hemoglobin A1c, peak VO_2_, Six-Minute Walk Test, step counts). Non-parametric tests (Mann Whitney and Kruskall Wallis tests) will be used for ordinal level data (i.e., International Physical Activity Questionnaire, Fatigue Assessment Scale, Montreal Cognitive Assessment, Hospital Anxiety and Depression Scale, Pittsburg Sleep Quality Index, Goal Attainment Scaling) or where a normal data distribution is not found. To control for baseline differences between groups, variables that are significantly different at baseline will serve as covariates in the analyses. Data will be analyzed on an intention-to-treat basis. Significant omnibus effects will be probed with t-tests, using the Bonferroni correction to control for multiple comparisons. Multiple regression will be conducted where appropriate to examine relationships among variables. Software will include Access and SAS version 9.1. Alpha level will be < 0.05.

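### PREVENT is taught in shared classes and USUAL CARE is not, yet the sample size assumes independent participants and the analysis names no class term; if outcomes correlate within classes, standard errors are too small and power for systolic blood pressure is below 80%

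*Protocol article*

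**What the plan says.** Randomization Procedures allocates individual participants to PREVENT or USUAL CARE. Group exercise component then states: "75-minute group exercise sessions, lead by a physiotherapist or kinesiologist, will be held twice weekly for 12 weeks". The education component, under Home exercise component, adds: "One 1.5-hour group session will be conducted weekly by a multi-disciplinary team of health professionals". USUAL CARE Intervention describes clinic assessment and return visits, three in total on average, and no classes.

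The Sample Size section states that "a sample size of 119 in each group will have 80% power to detect a difference in means of 4.9 mmHg". It takes the SD as 13.4 mmHg in both groups, and the figure is obtained "using a two group t-test with a 0.05 two-sided significance level". The only inflation is for 5% attrition, to 125 per group.

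Data management and analysis states, for the interval and ratio outcomes: "A mixed effects analysis of variance with repeated measures will be used to model the treatment effects". Significant omnibus effects are followed by Bonferroni-corrected t-tests. Ordinal or non-normal outcomes get Mann-Whitney and Kruskal-Wallis tests. No class or leader term is named.

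**The concern.** This is an individually randomized trial with group delivery in one arm, that is, a partially nested design. A PREVENT participant has about 24 exercise sessions (2 × 12) and 12 education sessions with the same peers and leaders. The PREVENT intervention section also lets participants help choose educational content, so what is delivered can differ between groups. Intervention audits treats consistency of delivery as something to be appraised. These are reasons to allow for correlation within a class.

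If that correlation is positive, the PREVENT mean is less precise than 119 independent values would make it. An analysis without a class term then understates the standard error of the difference and rejects too often under the null, and a valid test has less power than stated. The t-test calculation sits almost exactly at 80%, so it has no slack to absorb this.

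**Working it through.** **Inputs from the Sample Size section:** difference 4.9 mmHg, SD 13.4, two-sided alpha 0.05, 119 evaluable per arm, 5% attrition.

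**Assumptions, not in the document:** equal class size m between 5 and 15; ICC between 0.01 and 0.05; clustering in the PREVENT arm only; the same total SD in both arms.

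**1. The plan's own figure.** The exact noncentral t gives power of 79.9% at 118 and 80.2% at 119 per arm, so 119 is reproduced. By the normal formula, SE = 13.4 × √(2/119) = 1.737 and power = Φ(4.9/1.737 − 1.96) = 80.5%. For attrition, 119 × 1.05 = 125. The arithmetic is correct under independence.

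**2. Clustering in one arm.**
- Design effect in PREVENT: DE = 1 + (m − 1) × ICC.
- True SE = 13.4 × √((1 + DE)/119).
- Ratio of true to naive SE: R = √((1 + DE)/2).
- Power of a valid test = Φ(4.9/SE − 1.96).
- Type I error if clustering is ignored = 2 × (1 − Φ(1.96/R)).
- Evaluable n per arm for 80% power = (1 + DE) × (13.4 × (1.960 + 0.842)/4.9)², rounded up.

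Worked case, m = 10 and ICC 0.05: DE = 1 + 9 × 0.05 = 1.45. SE = 13.4 × √(2.45/119) = 1.923, and power = Φ(2.548 − 1.96) = 72.2%. R = √1.225 = 1.107, and type I error = 7.7%.

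| m | ICC | DE | R | Power, normal | Power, t with few-cluster df | Type I error if ignored | n per arm for 80% |
|---|---|---|---|---|---|---|---|
| any | 0 | 1.00 | 1.000 | 80.5% | 80.2% (ordinary t) | 5.0% | 118 |
| 5 | 0.01 | 1.04 | 1.010 | 79.8% | 78.7% | 5.2% | 120 |
| 5 | 0.05 | 1.20 | 1.049 | 76.7% | 75.5% | 6.2% | 130 |
| 10 | 0.01 | 1.09 | 1.022 | 78.8% | 76.7% | 5.5% | 123 |
| 10 | 0.05 | 1.45 | 1.107 | 72.2% | 69.3% | 7.7% | 144 |
| 15 | 0.01 | 1.14 | 1.034 | 77.8% | 74.3% | 5.8% | 126 |
| 15 | 0.05 | 1.70 | 1.162 | 68.0% | 62.9% | 9.2% | 159 |

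The t column uses Satterthwaite degrees of freedom with k = 119/m classes. For m = 15 and ICC 0.05, k = 7.9 and df = 2.70²/(1.70²/6.93 + 1/118) = 17.

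**3. What restoring 80% would take.** Dividing the last column by 0.95, the assumed range needs 127 (120/0.95) to 168 (159/0.95) randomized per arm by the normal formula, against 125 planned.

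**The case against.** The main objection is that everything turns on an ICC and a class size that the document does not give. At 5 per class and ICC 0.01 the normal-formula loss is under one percentage point. That stands, and it is why the consequence has to be worded conditionally. A reader might infer that the error bars are in fact too narrow and that 80% power is in fact not delivered. The document does not support that, because both need a within-class ICC above zero.

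Much of PREVENT is individual: goal meetings, therapy adjustment, exercise intensity set from each stress test, home exercise and monthly calls. Standardized training, common slides and audits limit differences between leaders. This argues for a low ICC. It does not remove peer effects or justify assuming zero without saying so.

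A mixed model can carry a class term, and a fuller protocol or analysis plan may specify one. This stands in part: the analysis model is incompletely described rather than shown to be wrong. It does not cover the sample size, which is fixed on independence, or the follow-up t-tests and rank tests, which in standard form carry no class effect. The repeated-measures model may also have more or less power than the t-test figure.

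Two further inferences go too far. Delivery at several sites does not by itself narrow the error bars: individuals are randomized, so site effects common to both arms largely cancel. Nor does the document say that classes are closed cohorts. Recruitment is continuous and entry may be rolling, so one fixed class per participant may not be definable.

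**Conclusion.** The point holds in conditional form. The Sample Size section assumes no class effect in an arm that is taught in classes, and the analysis as described makes no provision for one. Over the assumed range, power at 119 per arm is 79.8% to 68.0% by the normal formula, or 78.7% to 62.9% with few-cluster degrees of freedom. Type I error is 5.2% to 9.2% if clustering is ignored. At ICC 0 the type I error is nominal and the stated 119 is right. The size of the problem is therefore unknown, from negligible to material. The case for acting rests on low cost: Current study status says that patients are being enrolled, and class membership is easier to record now than to reconstruct later.

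**What to change.** 1. Record each PREVENT participant's class on the existing forms. With rolling entry, record the main class, or the leader and programme.
2. Add a class random effect, in the PREVENT arm only, to the planned mixed model. Treat each USUAL CARE participant as their own cluster and use small-sample degrees of freedom. Let the class effect act on the visits after randomization, because baseline is measured before allocation is revealed.
3. A random effect in the mixed model does nothing for the other tests. Use cluster-aware versions of the follow-up t-tests and rank comparisons, or label those results as assuming no class effect.
4. In Sample Size, state that the 80% holds only with no class effect, and give a power range over assumed class sizes and ICCs.

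The cost is one field on a form, one model term and one added sentence. Intervals will be slightly wider and the stated power lower. The degrees-of-freedom penalty applies even when the ICC is small: at 10 per class and ICC 0.01, power goes from 78.8% to 76.7%. No added patients are needed for this change. It makes the inference valid and the power statement honest, but it does not restore 80% if the ICC is appreciable.
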